**Figure 5. The dose adjustment plan for IFN- $\gamma$  for cohort 2.**

## 6.4 Stage 2: Donor Lymphocyte Infusion

### 6.4.1 Donor lymphocyte infusion

#### 6.4.1.1 Donor

- Donors are assessed and selected as per institutional guidelines.
- Donors are restricted to the original sibling or unrelated donor

#### 6.4.1.2 DLI product

- DLI will be prepared under the standard of care per institutional guideline.
- Cryopreserved GCSF-mobilized PBMCs collected at the time of transplant can be thawed and infused per institutional guideline and are considered as "DLI."
- If donor leukocytes are newly collected from the original donor, the donor will undergo the pre-apheresis assessment and apheresis for collection per institutional or the National Marrow Donor Program guideline. The collected cells will be stored in aliquots and cryopreserved for subsequent infusion.

#### 6.4.1.3 Dose and schedule of DLI

- In the absence of active grade II-IV GVHD or de novo grade III-IV, or progressive chronic GVHD requiring new systemic treatment or increased doses of current systemic treatment, the subject will receive the DLI at doses as per Table 1.
- Based on the response assessment (improvement in donor chimerism, change in malignant cells in blood or bone marrow) or toxicity, principally GVHD, patients may proceed to a second or third DLI (Table 3).

Table 3. Recommended dose escalation every 4 weeks of donor lymphocyte infusions. The actual dose of DLI will be determined by the subject's treating physician.

| DLI number             | DLI dose (CD3 + T cells/kg recipient weight $\pm$ 20%) |                                                |
|------------------------|-------------------------------------------------------------------|------------------------------------------------|
|                        | HLA matched sib                                                   | HLA matched unrelated                          |
| DLI #1 (starting dose) | $5 \times 10^6$                                                   | $5 \times 10^6$                                |
| DLI #2                 | $1 \times 10^7$                                                   | $1 \times 10^7$                                |
| DLI #3                 | Up to $1 \times 10^8$ per treating MD decision                    | Up to $5 \times 10^7$ per treating MD decision |

#### 6.4.2 Dose and schedule of IFN- $\gamma$ during the donor lymphocyte infusion stage

##### 6.4.2.1 For the subjects for whom donor leukocytes are available (cohort 1)

- After the first dose of DLI, the same dose of IFN- $\gamma$  as used pre-DLI for that patient will be continued three times a week for four weeks. If the subject develops intolerance to IFN- $\gamma$  during this period, we will reduce the frequency of IFN- $\gamma$  to once weekly.
- Four weeks after the first dose of DLI, the frequency of IFN- $\gamma$  will be tapered to once weekly, continued until the next DLI.
- A minimum of four weeks after the first dose of DLI, the subject will receive the second DLI, in the absence of active grade II-IV GVHD or de novo grade III-IV, or progressive chronic GVHD requiring new systemic treatment or increased doses of current systemic treatment per treating physician's determination. IFN- $\gamma$  will be continued at the same dose once weekly. There is an optional bone marrow aspirate if clinically indicated prior to the second DLI per the treating physician, and a research sample can be collected at that time.
- A minimum of 4 weeks after the second DLI, the subject will receive the third dose of DLI, in the absence of active grade II-IV GVHD or de novo grade III-IV, or progressive chronic GVHD defined by a requirement for new systemic treatment or increased doses of current systemic treatment. IFN- $\gamma$  will be continued at the same dose once weekly for

four more weeks. There is an optional bone marrow aspirate if clinically indicated before the third DLI, and a research sample may also be collected at that time.

- IFN- $\gamma$  will be continued once weekly until four weeks of the last dose of DLI or 12 weeks after the first dose of IFN- $\gamma$  whichever occurs later. If the subject develops intolerance to IFN- $\gamma$  during this period, we will discontinue IFN- $\gamma$
- At the end IFN- $\gamma$  treatment, the bone marrow aspirate is required ideally within seven days after the last dose of IFN- $\gamma$

#### 6.4.2.2 For the subjects for whom donor leukocytes are available (cohort 2)

- After the first dose of DLI, the same dose of IFN- $\gamma$  as used pre-DLI for that patient will be continued three times a week for four weeks. If the subject develops intolerance to IFN- $\gamma$  during this period, we will reduce the frequency of IFN- $\gamma$  to once weekly.
- A minimum of four weeks after the first dose of DLI, the subject will receive the second DLI, in the absence of active grade II-IV GVHD or de novo grade III-IV, or progressive chronic GVHD requiring new systemic treatment or increased doses of current systemic treatment per treating physician's determination. IFN- $\gamma$  will be continued at the same dose three times weekly. There is an optional bone marrow aspirate if clinically indicated prior to the second DLI per the treating physician, and a research sample can be collected at that time.
- 8 weeks after the first dose of IFN- $\gamma$  (or approximately 7 weeks after the first dose of DLI), the frequency of IFN- $\gamma$  will be tapered to once weekly, continued until the next DLI.
- A minimum of 4 weeks after the second DLI, the subject will receive the third dose of DLI, in the absence of active grade II-IV GVHD or de novo grade III-IV, or progressive chronic GVHD defined by a requirement for new systemic treatment or increased doses of current systemic treatment. IFN- $\gamma$  will be continued at the same dose once weekly for three more weeks. There is an optional bone marrow aspirate if clinically indicated before the third DLI, and a research sample may also be collected at that time.
- IFN- $\gamma$  will be continued once weekly until four weeks of the last dose of DLI or 12 weeks after the first dose of IFN- $\gamma$  whichever occurs later. If the subject develops intolerance to IFN- $\gamma$  during this period, we will discontinue IFN- $\gamma$
- At the end IFN- $\gamma$  treatment, the bone marrow aspirate is required ideally within seven days after the last dose of IFN- $\gamma$

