##### **1) The initial dose of IFN- $\gamma$**

- a. The first dose of IFN- $\gamma$  100 mcg will be administered on day 0 in the clinic.
  - b. The subject will continue self-injection of 100mcg, three times a week for two weeks (e.g., Monday, Wednesday, Friday or Tuesday, Thursday, Saturday)
- 2) 48 hours after the initial dose of IFN- $\gamma$  (up to 1 week)
- a. Bone marrow aspirate (no biopsy) will be performed for morphology, flow cytometry, and a research sample. (Cytogenetics/molecular testing only needed if clinically indicated to follow MRD.)
- 3) Two weeks after the initial dose of IFN- $\gamma$  (window: +/- 5 days)
- a. If 100 mcg per day three times a week is tolerated, the subject will continue IFN- $\gamma$  for the next two weeks.
  - b. If the subject is not tolerating at the dose of 100mcg per day three times a week for the first two weeks, decrease to 100 mcg two times a week for two weeks.
- 4) Four weeks after the initial dose of IFN- $\gamma$
- a. Subjects tolerating 100 mcg three times a week can proceed to DLI if eligible.
  - b. If the subject is not tolerating a given dose, it can be decreased to 100mcg two times a week for another two weeks (+/- 5 days). If tolerated, the patient would then be eligible to proceed to the DLI phase.
  - c. If 100 mcg two times per week is not tolerated, IFN- $\gamma$  will be discontinued, and the subject will be withdrawn from further on-study treatment. The subject may still proceed to DLI off study.

[figure not shown]

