**Figure 4. The dose adjustment plan for IFN- $\gamma$  for cohort 1.**

- Schedule of IFN- $\gamma$  and dose adjustment for cohort 2 (Figure 5)
- 1) The initial dose of IFN- $\gamma$
- a. The first dose of IFN- $\gamma$  100 mcg will be administered on day 0 in the clinic.
  - b. The subject will continue self-injection of 100mcg, three times a week for two weeks (e.g., Monday, Wednesday, Friday or Tuesday, Thursday, Saturday)

- 2) 48 hours after the initial dose of IFN- $\gamma$  (up to 1 week)
  - a. Bone marrow aspirate (no biopsy) will be performed for morphology, flow cytometry, and a research sample. (Cytogenetics/molecular testing only needed if clinically indicated to follow MRD.)
- 3) One week after the initial dose of IFN- $\gamma$  (window: - 3 days to + 7 days)
  - a. Subjects tolerating 100 mcg three times a week can proceed to DLI if eligible.
  - b. If the subject is not tolerating a given dose, it can be decreased to 100mcg two times a week for one week (+/- 5 days). If tolerated, the patient would then be eligible to proceed to the DLI phase.
  - c. If 100 mcg two times per week is not tolerated, IFN- $\gamma$  will be discontinued, and the subject will be withdrawn from further on-study treatment. The subject may still proceed to DLI off study.

[figure not shown]

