#### 6.6.1.3 Intolerance per the subject

- If the subject develops intolerance due to the expected adverse events (listed in Section 9.2.2), the dose may be reduced per treating physician or investigator discretion. If the symptoms are eventually attributed to other cause or resolve, then the dose may be increased again, per treating physician or investigator discretion.

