### 6.7 Criteria for Discontinuation of IFN- $\gamma$

Specific conditions that will require discontinuation of IFN- $\gamma$  are as follows:

- Pregnancy
- New-onset grade 3 or 4 acute GVHD
- Progression of disease which requires immediate cytoreduction chemotherapy or other therapy per treating physician's determination
- Immediate hypersensitivity reaction associated with a study injection
- Intercurrent CTCAE grade 3 or 4 illness or organ dysfunction (other than cytopenias and electrolyte abnormalities) that does not resolve to grade  $\leq$  1 within two weeks
- The study site PI or treating physician assesses that it is not in the best interest of the subject to continue on the study.
- The dose of IFN- $\gamma$  can be discontinued anytime based on the clinical status of the subject at the treating physician's discretion. If IFN- $\gamma$  is not given for six doses, the subject will be withdrawn from further on-study treatment.

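### A patient reduced to twice-weekly IFN-gamma in stage 1 may go on to DLI, but Sections 6.4.2.1 and 6.4.2.2 then set three times a week, with no twice-weekly branch

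*Protocol*

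**What the plan says.** Stage 1 starts everyone at 100 mcg three times a week (Section 6.3.2). De-escalation is by frequency (Section 2.2), and each printed step keeps the injection at 100 mcg.

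- Cohort 2, Section 6.3.2, step 3b: for a patient not tolerating the regimen, "it can be decreased to 100mcg two times a week for one week".
- Cohort 1, Section 6.3.2, step 4b: "If the subject is not tolerating a given dose, it can be decreased to 100mcg two times a week for another two weeks".
- In both cohorts a patient who tolerates twice weekly becomes eligible for the DLI phase. IFN-gamma is stopped under this scheme only if twice weekly also fails (steps 3c and 4c).

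Stage 2 is then written as follows.

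- Sections 6.4.2.1 and 6.4.2.2, first bullet (same sentence): after the first DLI, the same dose of IFN-gamma "as used pre-DLI for that patient will be continued three times a week for four weeks". A patient who becomes intolerant in this period drops to once weekly.
- Section 6.4.2.2, second bullet, around the second DLI: IFN-gamma "will be continued at the same dose three times weekly". The taper to once weekly comes 8 weeks after the first IFN-gamma dose.
- The synopsis for cohort 2 likewise gives three times a week for seven weeks after the first DLI.

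Section 6.6.1.3 covers reversing a reduction made for expected adverse events. If the symptoms resolve or prove to have another cause, "then the dose may be increased again, per treating physician or investigator discretion".

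**The concern.** The protocol deliberately creates a group of patients who enter stage 2 on twice weekly, and then gives that group no schedule. Followed literally, Section 6.4.2.2 raises them to the frequency they did not tolerate, and the trigger is the first DLI rather than recovery. Section 6.6.1.3 treats a re-increase as a discretionary decision with conditions; Section 6.4.2.2 makes it the default.

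Two things are at stake. One is the patient: GVHD is the protocol's stated main safety concern (Section 2.2), and exposure would rise as donor T cells are infused. The other is how the data are read. The second primary safety endpoint is the adverse events of IFN-gamma given with DLI (Sections 1.1.3.2 and 8.1.1). If one site re-escalates and another keeps twice weekly, the exposure behind those events depends on how the site read the sentence.

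**Working it through.** **1. What the sentence can mean.** Two readings are available.

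- Dose means the amount per injection. Stage 2 uses it this way elsewhere: in Section 6.4.2.1, third bullet, IFN-gamma "will be continued at the same dose once weekly". The amount is 100 mcg for everyone, so the sentence sends a twice-weekly patient back to three times a week.
- Dose includes frequency, as in step 3b of the cohort 1 schedule in Section 6.3.2. The sentence then asks for the twice-weekly regimen to be given three times a week, which contradicts itself.

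Neither reading gives a usable instruction for a twice-weekly entrant.

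**2. Whether another section supplies the rule.**

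- Section 5.2.3 allows departures from three times weekly by protocol guidance on tolerability, which leads back to the text in question.
- Section 6.6.1 gives criteria for reduction, and 6.6.1.3 gives discretion. Neither states a twice-weekly schedule after DLI.
- Section 6.7 lets the physician stop IFN-gamma at any time but gives no reduced schedule.
- Figures 4 and 5 are not reproduced in the text available. They may draw a twice-weekly path, but the sentences in 6.4.2 would then conflict with the figures.

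**3. Who is affected.**

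- Section 6.4.1.3 gives DLI only "In the absence of active grade II-IV GVHD or de novo grade III-IV, or progressive chronic GVHD requiring new systemic treatment" (a rise in existing systemic therapy counts as well).
- Section 6.7 stops IFN-gamma for "Intercurrent CTCAE grade 3 or 4 illness or organ dysfunction (other than cytopenias and electrolyte abnormalities) that does not resolve to grade" (the threshold is grade 1 or less, reached inside two weeks).
- The patients left are mainly those reduced for expected adverse events, for resolved or grade I GVHD, or for organ toxicity that has resolved or is still inside that two-week window. The window can still be open in cohort 2, where twice weekly is tried for only one week before DLI.

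**4. Size, per reduced patient.** Inputs: 100 mcg per injection; 3 or 2 injections a week (Section 6.3.2); four weeks stated after DLI (Sections 6.4.2.1 and 6.4.2.2); taper at week 8, that is day 56 (Section 6.4.2.2); end-of-stage-1 visit at day 7, with the first DLI within two weeks of it (Section 6.5.2.4). Visit windows are ignored.

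- Weekly exposure: 3 × 100 = 300 mcg against 2 × 100 = 200 mcg; 300 / 200 = 1.5, or +50%.
- Stated four weeks: 4 × 3 = 12 against 4 × 2 = 8 injections, a difference of 4 (1,200 against 800 mcg).
- Cohort 2 to the taper, earliest nominal DLI: day 7 + 7 days on twice weekly = day 14; 56 − 14 = 42 days = 6 weeks; 18 against 12 injections (+6).
- Cohort 2 to the taper, latest nominal DLI: day 7 + 14 = day 21; 56 − 21 = 35 days = 5 weeks; 15 against 10 injections (+5).
- If a site instead follows Section 6.5.2.5, which moves to once weekly at about 14 days after DLI: 2 × 3 = 6 against 2 × 2 = 4 injections (+2).

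The synopsis's seven weeks (7 × 3 = 21 against 7 × 2 = 14) does not fit a reduced patient at nominal times, because the extra week on twice weekly pushes DLI past day 7.

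**The case against.** The strongest reply is that the sentence was meant to carry the patient's own regimen forward. Section 6.3.2 uses dose loosely enough to include frequency, the sentence speaks of continuing, and the reference to that particular patient does no work if the amount never varies. On this view three times a week is simply the usual case, left unadapted for the exception. That may well be the intent, but the printed frequency still contradicts it, and a site has to choose which half of the sentence to follow.

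The reply also points to clinical discretion. Sections 5.2.3, 6.6.1 and 6.7 make it unlikely that a physician would feel bound to restart a frequency a patient still cannot tolerate. Flu-like symptoms cluster in the first week (Section 6.9.2), so many re-increases would be reasonable under 6.6.1.3. Patients keep an injection diary (Section 6.3.2), so actual exposure should be recoverable. The analysis is descriptive (Section 8.1.1.1), so no error rate, boundary or sample size changes.

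All of this stands and limits the harm. The +2 figure also comes from a separate inconsistency, the early taper in 6.5.2.5, and is only a lower bound. But discretion does not write the missing rule, and a diary records divergent exposure without preventing it.

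**Conclusion.** The point holds: the stage 2 text is wrong as written for any patient who enters DLI on twice weekly. For such a patient the two readings differ by 100 mcg a week (+50%), which is 4 injections over the stated four weeks. In cohort 2 the difference up to the week 8 taper is 5 to 6 injections at nominal visit times, or 2 if the earlier taper in 6.5.2.5 is followed.

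The number of reduced patients is not known and may be zero. Cohort 2 plans only three to six DLI recipients (synopsis and Section 8.2.1), so even one patient handled differently would be a visible share of the safety summary. The synopsis says monotherapy safety was confirmed in cohort 1, so the text that matters now is 6.4.2.2. Section 6.4.2.3, for patients without donor cells, can be read as covering only those who tolerate three times a week, and is not counted as a contradiction. This should be corrected, but it does not threaten the design.

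**What to change.** Reword three sentences.

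- Sections 6.4.2.2 and 6.4.2.1, first bullet: *Following the first DLI, give IFN-gamma 100 mcg for four weeks at the frequency the patient tolerated before DLI (three or two times a week).*
- Section 6.4.2.2, second bullet: *Continue IFN-gamma at an unchanged dose and frequency.*

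Keep once weekly as the step for new intolerance in stage 2, and leave any return to three times a week to the discretion already in 6.6.1.3. For clarity, add matching words to 6.4.2.3 (100 mcg at the frequency currently tolerated, three or two times a week) and to the synopsis (two times a week if reduced in stage 1). Check that Figures 4 and 5 agree. The cost is a few words in an amendment, with no extra visits, samples or patients.

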Cohort 2: As we confirmed the safety of IFN- $\gamma$  monotherapy in the first cohort, we will evaluate a second cohort wherein we will shorten IFN- $\gamma$  monotherapy (stage 1) to 1 week before DLI. In stage 1, we will assess the safety a fixed-dose of IFN- $\gamma$  (100mcg subcutaneously three times per week) for one week. The bone marrow biopsies will be performed before and no earlier than 48 hours to 1 week after the first dose of IFN- $\gamma$  to assess malignant blasts for an IFN- $\gamma$  response. In stage 2, subjects who have tolerated IFN- $\gamma$  will receive DLI in a dose-escalating manner. IFN- $\gamma$  will be continued three times a week for seven weeks after the first dose of DLI, followed by once-weekly IFN- $\gamma$  for four weeks. The patients will be off treatment after a 12 week-course of IFN- $\gamma$  with a repeat bone marrow biopsy at this point. The clinical outcomes will be monitored at six months after the first dose of IFN- $\gamma$  and then the subjects will be off study. Figure 2 summarizes the study design for cohort 2.

Sample size: Our goal is to have at least three patients receive at least one dose of DLI. For example, if the first three patients all complete stage 1 and stage 2, this initial pilot study would be completed with three patients. We estimate enrolling six total patients, but not likely more than nine, as some patients may not be able to complete the study due to the development of rapid disease progression or unavailability of DLI. Based on the nature of the transplant populations at our centers, we estimate accrual will be completed within six months.

For cohort 2, we aim to enroll six patients receiving IFN- $\gamma$  and at least one dose of DLI.

[figure not shown]

**Figure 1. Study Design of Cohort 1:** The figure outlines the scheme of how to administer IFN- $\gamma$  and subsequent donor lymphocyte infusions after enrollment. Biospecimens will also be collected, as shown. BM: bone marrow aspirates, DLI: donor lymphocyte infusion, IFN- $\gamma$ : interferon-gamma, PBMC: peripheral blood mononuclear cells

[figure not shown]

**Figure 2. Study Design of Cohort 2:** The figure outlines the scheme of how to administer IFN- $\gamma$  and subsequent donor lymphocyte infusions after enrollment. Biospecimens will also be collected, as shown. BM: bone marrow aspirates, DLI: donor lymphocyte infusion, IFN- $\gamma$ : interferon-gamma, PBMC: peripheral blood mononuclear cells

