- Clinical safety monitoring: Any reaction or symptoms related to the prior doses of IFN- $\gamma$  and will be assessed specifically focusing on active grade II-IV GVHD or de novo grade III-IV, or progressive chronic GVHD
- Laboratory monitoring: CBC with differential, chemistry panel (Na, K, Cl, CO2, creatinine, glucose, urea nitrogen, phosphorus, magnesium, albumin, calcium, LDH, uric acid), hepatic (alkaline phosphatase, ALT, AST, and total bilirubin) panel
- The subsequent doses of IFN- $\gamma$  will be administered after the safety assessment.
- If DLI is available, the first dose of DLI will be infused within two weeks from this visit.

6.5.2.5 Protocol visit #4: Stage 2 first safety assessment, 21 days (+/- 5 days) after the first dose of IFN- $\gamma$ , or 14 days (+/- 5 days) after the first dose of DLI.

- Clinical safety monitoring: Any reaction or symptoms related to the IFN- $\gamma$  or DLI will be assessed, specifically focusing on active grade II-IV GVHD or de novo grade III-IV, or progressive chronic GVHD
- Laboratory monitoring: CBC with differential, chemistry panel (Na, K, Cl, CO2, creatinine, glucose, urea nitrogen, phosphorus, magnesium, albumin, calcium, LDH, uric acid), hepatic (alkaline phosphatase, ALT, AST, and total bilirubin) panel
- The subsequent frequency IFN- $\gamma$  will be reduced to once-weekly dosing for four more weeks.

6.5.2.6 Protocol visit #5: Stage 2 follow up safety assessment, 35 days (+/- 5 days) after the first dose of IFN- $\gamma$ , or 28 days (+/- 5 days) after the first dose of DLI

- Clinical safety monitoring: Any reaction or symptoms related to the IFN- $\gamma$  or DLI will be assessed, specifically focusing on active grade II-IV GVHD or de novo grade III-IV, or progressive chronic GVHD
- Laboratory monitoring: CBC with differential, chemistry panel (Na, K, Cl, CO2, creatinine, glucose, urea nitrogen, phosphorus, magnesium, albumin, calcium, LDH, uric acid), hepatic (alkaline phosphatase, ALT, AST, and total bilirubin) panel
- STR chimerism of bone marrow (if collected) and peripheral blood (whole blood, or CD3 and myeloid)
- Research sample collection: 30 mL of peripheral blood (10 mL green top heparin tube x

3 tubes) will be collected.

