- Optional bone marrow aspirates (no biopsy) will be performed for morphology, flow cytometry, and research sample (10ml) if clinically indicated. Cytogenetics/molecular testing only needed if clinically indicated to follow MRD if clinically indicated.
- If the second or third dose of DLI is available, the DLI will be infused at minimal 4 weeks of interval in the absence of active grade II-IV GVHD or de novo grade III-IV, or progressive chronic GVHD requiring new treatment or increased doses of current treatment per treating physician's determination.
- There is an optional bone marrow aspirate if clinically indicated before the second or the third DLI per the treating physician, and research sample (10mL in green top heparin tube) will be collected.

6.5.2.7 Protocol visit #6: Stage 2 follow up safety assessment, 56 days (+/- 7 days) after the first dose of IFN- $\gamma$  (= approximately 49 days +/- 7 days after the first DLI or 21 days +/- 7 days after the second DLI)

- Clinical safety monitoring: Any reaction or symptoms related to the IFN- $\gamma$  or DLI will be assessed, specifically focusing on active grade II-IV GVHD or de novo grade III-IV, or progressive chronic GVHD
- Laboratory monitoring: CBC with differential, chemistry panel (Na, K, Cl, CO2, creatinine, glucose, urea nitrogen, phosphorus, magnesium, albumin, calcium, LDH, uric acid), hepatic (alkaline phosphatase, ALT, AST, and total bilirubin) panel
- Research sample collection: 30 mL of peripheral blood (10 mL green top heparin tube x 3 tubes) will be collected.
- Optional bone marrow aspirates (no biopsy) will be performed for morphology, flow cytometry, and research sample (10ml) if clinically indicated. Cytogenetics/molecular testing only needed if clinically indicated to follow MRD if clinically indicated.
- If the third dose of DLI is available, the DLI will be infused at minimal 4 weeks of interval in the absence of active grade II-IV GVHD or de novo grade III-IV, or progressive chronic GVHD requiring new treatment or increased doses of current treatment per treating physician's determination.
- There is an optional bone marrow aspirate if clinically indicated before the third DLI per the treating physician, and research sample (10mL in green top heparin tube) will be collected.

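### Cohort 2 visit #4 orders once-weekly IFN-γ from about day 21 without condition, against the week-8 taper in section 6.4.2.2 and the synopsis

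*Protocol*

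**What the plan says.** Three places in the protocol set the IFN-γ frequency for cohort 2 after the first DLI.

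- **Synopsis, Cohort 2.** After one week of monotherapy, IFN-γ "will be continued three times a week for seven weeks after the first dose of DLI", then once weekly for four weeks, for a 12-week course.
- **Section 6.4.2.2.** After the first DLI, IFN-γ "will be continued three times a week for four weeks" (first bullet). At the second DLI it "will be continued at the same dose three times weekly" (second bullet). The taper to once weekly comes 8 weeks after the first IFN-γ dose ("or approximately 7 weeks after the first dose of DLI), the frequency of" IFN-γ is tapered; third bullet). In the first bullet, an earlier cut to once weekly is tied to intolerance. The fourth bullet gives three further weeks of weekly dosing after a third DLI. The fifth says IFN-γ "will be continued once weekly until four weeks of the last dose of DLI or 12 weeks after the first dose of" IFN-γ, whichever is later.
- **Section 6.5.2.5, visit #4.** The visit is headed "Protocol visit #4: Stage 2 first safety assessment, 21 days (+/- 5 days) after the first dose of" IFN-γ, or 14 days after the first DLI. Its last bullet says the frequency "will be reduced to once-weekly dosing for four more weeks". Intolerance is not mentioned.

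Visit #6 in section 6.5.2.7 is where the week-8 taper falls (day 56, "approximately 49 days +/- 7 days after the first DLI or 21 days +/- 7 days after the second DLI"), but it gives no IFN-γ instruction. Appendix D marks IFN-γ through V6 (day 56) and refers to the protocol without stating a frequency. The visit #4 sentence also stands at cohort 1 visit #5 (section 6.5.1.6), which covers both DLI and non-DLI subjects.

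**The concern.** Visit #4 is a direct dosing instruction that contradicts the section written to set dose and schedule. It falls two weeks before the nominal second DLI, so the two versions differ most around that infusion. Section 2.2 names GVHD as the primary safety concern.

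Section 8.1.1 makes adverse events of IFN-γ with concurrent DLI a primary safety endpoint. Section 8.2.1 plans at least three cohort 2 patients with IFN-γ and DLI and up to six enrolled; the synopsis aims for six. At that size, one or two patients dosed by the visit list and the rest by section 6.4.2.2 would leave a safety table that describes no single regimen. The injection diary (section 6.3.2) records what was given. It does not settle what should have been given.

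**Working it through.** **Inputs, nominal schedule.** First IFN-γ dose day 0; first DLI day 7 (V3); visit #4 day 21; second DLI day 35 (V5); visit #6 day 56; end of course day 84 (week 12). The days come from Appendix D and section 6.5.2. No reduction for intolerance is assumed.

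**Formula.** Planned injections = 3 × (weeks at three per week) + 1 × (weeks at one per week).

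**The plan's own figure.** Synopsis: 1 + 7 + 4 = 12 weeks, reproduced. Section 6.4.2.2 gives the same step-down at week 8: 3 × 8 + 1 × 4 = 28 injections.

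**Following visit #4.** Three-times-weekly dosing stops at day 21 (week 3).

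| Reading | Calculation | Injections | Shortfall against 28 |
|---|---|---|---|
| Weekly dosing runs on to week 12 | 3 × 3 + 1 × 9 | 18 | 10 (36%) |
| Four weeks taken literally, ending day 21 + 28 = 49 | 3 × 3 + 1 × 4 | 13 | 15 (54%) |

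The literal reading ends in week 7, short of the 12-week course and of the IFN-γ mark at V6 (day 56) in Appendix D.

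**Where the gap lies, first reading.** Day 21 to 35: 6 injections against 2. Day 35 to 56: 9 against 3. Together: 15 against 5.

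**Sensitivity to timing.**
- Visit #4 window, day 16 to 26, weekly dosing to week 12: 3 × 16/7 + 68/7 = 16.6, and 3 × 26/7 + 58/7 = 19.4. That is about 17 to 19 injections instead of 28.
- First DLI delayed to day 21 (section 6.5.2.4 allows two weeks from visit #3), with visit #4 timed 14 days later at day 35. From day 35 to the day-56 taper of section 6.4.2.2 there are 3 weeks: 9 against 3. With weekly dosing to week 12 the shortfall is then 6 instead of 10.

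**Related wording in section 6.4.2.2.** On the four-week minimum interval, a third DLI falls no earlier than day 35 + 28 = 63 on this schedule. The fourth bullet then ends dosing at day 63 + 21 = 84 and the fifth at day 63 + 28 = 91. Both lie in the visit #7 window (day 84 ± 14 = day 70 to 98), but they are different rules.

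**Cohort 1 non-DLI subjects.** Section 6.4.2.3 gives two more weeks three times weekly after four weeks of stage 1 (to week 6), then once weekly to week 12, which is six weeks. The sentence at visit #5 gives four, ending at week 10.

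**The case against.** The strongest reply is that the intended regimen is not in real doubt. Section 6.4.2 is headed as the dose and schedule section and agrees with the synopsis on the nominal schedule. Visit #4 is the outlier, and read literally it breaks the 12-week course. The sentence suits a non-DLI step-down in cohort 1 better, so it looks carried over. The error lowers exposure. The safety analysis is descriptive (section 8.1.1.1), and individual schedules already vary through reduction and discontinuation. The post-dose marrow sample is taken 48 hours to one week after the first dose, before visit #4, so that pre/post comparison for the biological endpoint is untouched.

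All of this stands and limits the consequence. It does not remove the contradiction: the visit #4 order is unconditional, and no text at hand gives section 6.4.2.2 precedence over the visit list. Figure 2, the cohort 2 scheme, is not reproduced in the text at hand, so it could not be checked.

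The four-week wording in the first bullet of section 6.4.2.2 is a lesser matter. For a patient who has the second DLI at four weeks, the bullets can be read in sequence without a gap. Without a second DLI at that point, the weeks up to the taper are not covered explicitly. The once-weekly reduction rule is also tied to the four-week period.

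Three stronger readings might be inferred, and the documents do not support them:
- **A fixed shortfall of ten injections, whatever the end date.** It is 15 if the four weeks are literal, and smaller against section 6.4.2.2 if the first DLI is late.
- **Cohort 2 treated less intensively after DLI than cohort 1.** Two weeks against four sets cohort 2's visit list against cohort 1's treatment section. Like for like, the visit lists give two weeks in both cohorts, and the treatment rules give seven (cohort 2) against four (cohort 1).
- **Patients were in fact under-dosed.** The protocol shows only what is instructed, not what was given.

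**Conclusion.** The contradiction holds. Cohort 2 visit #4 steps IFN-γ down at about week 3, five weeks before the week-8 taper in section 6.4.2.2 and the synopsis, and nothing in the text at hand corrects it. On the nominal schedule, for a patient not reduced for intolerance, 28 planned injections become 18 or 13, depending on how the four-week phrase is read. The figures assume the first DLI at day 7 and visit #4 at day 21. This is a faulty operative dosing instruction that bears on a primary safety endpoint. It should be corrected before further cohort 2 dosing, but it does not call the design or the sample size into question.

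**What to change.** 1. **Section 6.5.2.5, visit #4:** delete the last bullet. State that IFN-γ continues per section 6.4.2.2, three times weekly unless reduced for intolerance, until 8 weeks after the first dose.
2. **Section 6.5.2.7, visit #6 (day 56):** add the taper to once weekly, with the end of dosing per section 6.4.2.2.
3. **Section 6.4.2.2:** make the first bullet run to the week-8 taper, so that the schedule and its intolerance rule cover the whole three-times-weekly phase. Align the three weeks in the fourth bullet with the end rule in the fifth (four weeks after the last DLI or 12 weeks after the first IFN-γ dose, whichever is later).
4. **Section 6.5.1.6, cohort 1 visit #5, only if cohort 1 treatment is still open:** limit the sentence to non-DLI subjects, and replace its four-week limit with completion of 12 weeks, per section 6.4.2.3.

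This restores 28 planned injections over 12 weeks on the nominal schedule. The cost is wording edits in three sections, and in a fourth if cohort 1 is open. No visits, data or patients are added.
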